#### Gait Assessments

Participants will be given standardized instructions and a visual demonstration of the different gait task. Participants will then be asked to perform three single-task trials and three dual-task trials. The single task trials consist of walking the length of the mat at a self-selected pace. For the dual-task trials, participants will be asked to walk while counting aloud backward from one hundred by ones. This dual-task condition is selected based on previous research which demonstrated that counting backwards requires both working memory and attention [49]. Participants will be instructed to pay attention to both gait and the cognitive task; if a participant stops either task during the trial they will be prompted to continue. Allowing both gait and cognitive task to vary has previously been shown to provide a better representation of what happens naturally [8,50].

#### Balance Confidence Scale

Balance confidence will be evaluated using the Activities-Specific Balance Confidence Scale (ABC) [39]. Respondents self-rate their confidence about their balance while performing a series of daily tasks on this 16-item questionnaire. The described tasks range in difficulty from those of basic daily living (e.g. walking around the house, going up and down stairs), to more difficult tasks generally performed in the community (e.g. walking in crowded areas like shopping centres, using escalators). Respondents are asked to rate their confidence on a scale from 0% (no confidence) to 100% (complete confidence) based on the following cue question: "How confident are you that you will not lose your balance or become unsteady when you [list of items follows]." The scale's wide range of item difficulty makes it well suited to assessing balance as a construct in populations with varying levels of functioning, including high-functioning community living seniors. This scale has been validated in previous studies as a marker of risk of falling [39,51].

#### Balance Sway Test

Balance will be quantified as body sway using a Digital Balance Platform available in our service (Bertec Inc.). Displacements of the body in frontal and saggital direction will be recorded in millimetres. Peak-to-peak amplitude (maximum displacement of center of pressure, CoP) in the saggital and frontal direction will be calculated. Sway area will be calculated by multiplying the maximal frontal diameter with maximal saggital diameter following the method validated by Lord and colleagues [52]. Testing will be performed with subjects standing directly on the balance plate and standing on a foam rubber mat placed on the balance plate, with both measures being repeated with the participants having their eyes open and closed.

#### Falls

A fall is defined as 'an unintentionally coming to rest on the ground, floor, or other lower level and not due to a seizure or an acute stroke [63]. Recurrent falls are defined as two or more events in a six-month period during the trial. An absolute reduction of 10 points in the rate of falls is expected in intervention group after six months of follow-up (20% in the control to 10% in the intervention). Because falls tend to be forgotten if no injuries are involved, a fall calendar enabling prospective assessment will be implemented [64]. At the baseline session, participants will receive a fall calendar and instructed in its use (i.e. they will be asked to record every day whether they have had a fall). Each monthly calendar page detaches along a perforation and becomes a postage-paid postcard addressed to the study office. Calendar pages each have a unique study ID number and no identifying information. If a calendar is not received by two weeks into the following month, or is missing or incomplete the research assistant will contact the participant by phone and together they will complete the page. Participants who indicate one or more fall will be contacted by study staff and interviewed about the circumstances and outcomes of the falls. These methods have been used locally in previous research [47,48].

#### Data acquisition of the quantitative gait variables

GAITRite software Version 3.8 will be used to process the footstep data using an algorithm for light and short footsteps as older individuals with cognitive problems may be more likely to slow down or hesitate while dual-tasking. Participants will be instructed to wear comfortable clothes and shoes. Gait variability will be analyzed in terms of stride time variability, and reported as coefficient of variation [27]. Validity and reliability of the GAITRite system has been established in older adults with memory problems by ourselves [53] and other research groups [54-56].

### Sample size determination

Sample size determination is based on our primary outcomes and using the values from the pilot data described above. We expect a 10% improvement in gait velocity (G-vel), measured in cm/s (effect size of 0.10 m/s, from 1.0 m/s to 1.10 m/s), and a reduction in gait variability (G-var) (stride time variability) of 10% as assessed by decreases in standard deviation and coefficient of variation. These expected changes are based on our preliminary data which showed that mean G-vel increased by 15% after one month of treatment and these changes were sustained and improved in the 4 months follow up [38]. In this study, we found that the mean stride time at usual gait was 1190 ± 266 milliseconds (ms), after one month of treatment was 1053 ± 178 ms, and after 4 month was 999 ± 112 ms. The absolute reduction of the mean group CoV was 11 points (from 22.4% to 11.3%). Therefore, it is reasonable to expect similar improvements in our proposed study with a larger sample. Thus, in order to detect a group reduction of variability of 10% with a type II error of 0.20, 69 participants in each arm will be needed for the final analysis; assuming a 5 percent drop-out rate (which was seen after 6 months in two previous studies testing medications on MCI), 75 per arm participants will need to be recruited. This sample will also allow the detection of a 10% difference in the mean scores of the ABC, which is considered clinically significant. While we will not have sufficient power for a definitive analysis of changes in fall rate or risk, we will be able to compare changes in the mean values of the primary outcomes with between-group differences in fall rate. This will add mechanistic evidence that changes in fall rate are due to changes in gait parameters, and will provide a point estimate needed for the sample size calculations for a future trial powered to detect a reduction in falls as a primary endpoint.

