A sensitive measure of gait performance is gait variability, defined as the stride-to-stride variation in time [27]. This measure quantifies the automaticity of gait, with greater variability indicating less rhythmicity and a more unstable gait pattern. Evaluating gait variability is an accurate methodology to identify subtle changes in walking due to pathological conditions or disease. For instance, cognitively normal older adults have low gait variability; however, high gait variability has been described in Parkinson's disease, Alzheimer disease, and has been associated with high risk of future falls and mobility decline [28]. Additionally, previous studies have demonstrated that gait variability may serve as a clinically relevant parameter in the evaluation of mobility, and may be a responsive measure for different interventions in fall prevention [29].

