### Pilot data and Rationale

As a proof of principle for this proposed RCT, we assessed the effect of donepezil, over four months of treatment, on gait using an electronic walkway (GAITRite System) in six individuals with AD [38]. An increase in gait velocity and a reduction in gait variability were seen following cognitive enhancer treatment. In brief, participants with AD taking donepezil increased their mean gait velocity (G-vel) after one month (from 89.7 ± 11 to 106.9 ± 22, *p *= .045) under a single-tasking condition. These increases were sustained and improved after four months, suggesting a dose-response pattern as shown in Figure 2. Gait variability (G-var), assessed as coefficient of variation of stride time, decreased during follow-up (single-task from 22.3 to 11.30, *p *= .04). Since it is known that gait performance declines over time in older people, we compared these results with observational data from eight comparison individuals with MCI and found that the MCI group experienced a reduction of gait velocity over time. (Figure 2)

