### Outcomes measures

#### Primary outcomes

1. Improvements in gait velocity (cm/second) at month six

2. Reduction in gait variability assessed as standard deviation (SD) and coefficient of variation (CoV) at month 6.

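### The 80% power claimed for gait variability at 69 per arm is unsupported: the pilot CoV is probably the spread of stride time between people, and no SD of individual CoVs is given

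*Protocol article*

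**What the plan says.** The Background section on dual-tasking defines the quantity as "gait variability, defined as the stride-to-stride variation in time", a property of one person's walking. The second primary outcome is "Reduction in gait variability assessed as standard deviation (SD) and coefficient of variation (CoV) at month 6". The section on data acquisition adds: "Gait variability will be analyzed in terms of stride time variability, and reported as coefficient of variation".

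Pilot data and Rationale describes six people with Alzheimer's disease and states: "Gait variability (G-var), assessed as coefficient of variation of stride time, decreased during follow-up (single-task from 22.3 to 11.30", with p = .04. Sample size determination gives the pilot stride times: "mean stride time at usual gait was 1190 ± 266 milliseconds (ms), after one month of treatment was 1053 ± 178 ms", and 999 ± 112 ms at four months. It continues: "The absolute reduction of the mean group CoV was 11 points (from 22.4% to 11.3" per cent). It then concludes that "in order to detect a group reduction of variability of 10% with a type II error of 0.20, 69 participants in each arm" are needed.

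Statistical Analysis defines CoV as SD over mean, times 100, without saying whose SD and mean. It plans linear regression, favours the baseline value as a covariate, and sets two-sided significance at 0.05.

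**The concern.** Two different quantities appear under one name. Stride-to-stride CoV is computed within a person, and the trial would compare its average between arms. The pilot CoV looks like the SD of stride time across the group divided by the group mean. If so, its fall shows six people becoming more alike in stride time. It says nothing about whether any of them walked more regularly.

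To size a two-arm comparison of individual CoVs, one needs how much those CoVs differ between people, or the SD of their change. Sample size determination gives neither, yet states a specific n and 80% power for this outcome. A null result for variability could then be read as an adequately powered negative when nothing in the article supports that. Because Statistical Analysis does not say that CoV is taken within each participant, a group-level CoV could also recur in the trial analysis.

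**Working it through.** **Inputs.** Pilot stride times: 1190 ± 266 ms at baseline, 1053 ± 178 ms at one month, 999 ± 112 ms at four months. Pilot CoV: 22.4% to 11.3% (Sample size determination) or 22.3 to 11.30 (Pilot data and Rationale). Effect 10%, type II error 0.20, 69 per arm, 1:1 allocation. Two-sided alpha of 0.05 comes from Statistical Analysis.

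**1. What the pilot CoV is.**
- Baseline: 266/1190 = 22.35%. Rounding of the inputs allows 22.30% to 22.40%, which covers both printed values.
- Four months: 112/999 = 11.21%. Rounding allows 11.16% to 11.27%, which agrees with 11.3% at one decimal but falls just short of 11.30.

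**2. Reproducing 69.** The article names no formula. One that returns the figure takes 22.35% as the between-person CV of mean stride time and a 10% fall in that mean, on the log scale with the normal approximation:
- SD of log = √ln(1 + 0.2235²) = 0.2208; difference = −ln 0.9 = 0.1054
- n per arm = 2 × (1.960 + 0.842)² × 0.2208² / 0.1054² = 68.95, so 69

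Other variants on mean stride time come near but miss: 71 with a constant-CV formula, and 79 on the raw scale (119 ms, SD 266 ms). Readings that treat the group CoV itself as the outcome are far off: 710 per arm for an F-test of a 10% lower group SD, and 178 per arm if 22.4% and 11.3% are compared as proportions.

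**3. What 69 per arm needs for the stated outcome.** Treat individual CoV on the log scale with a ratio of 0.90 and a two-sample t-test without covariates (the log scale is chosen here; the article does not specify it). At 69 per arm, 80% power needs a standardised difference of 0.480, so the SD of log CoV may be at most 0.1054/0.480 = 0.22. The article gives no such SD.

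**4. Illustration with assumed SDs** (none comes from the article):

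| SD of log CoV (assumed) | Standardised difference | Power at 69 per arm, unadjusted |
|---|---|---|
| 0.30 | 0.351 | 54% |
| 0.40 | 0.263 | 34% |
| 0.50 | 0.211 | 23% |

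With the baseline value as covariate and an assumed correlation of 0.7, an SD of 0.30 becomes 0.30 × √(1 − 0.7²) = 0.214. The standardised difference is then 0.492 and power is 82%.

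**5. The other primary outcome.** For gait velocity, 10 cm/s with the one-month pilot SD of 22 gives a standardised difference of 0.455 and about 76% power at 69 per arm, unadjusted; 80% needs 77 per arm. With the baseline pilot SD of 11, 20 per arm suffice.

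**The case against.** The article never says whose SD the ± values are. Its phrase for the pilot figure could mean the average of individual CoVs, and the method stands in a cited pilot report that is not shown. The four-month match is good but not exact. These points stand, so the between-person reading is probable and not proved. They do not rescue the power claim: if the ± values are average within-person SDs, the spread of individual CoVs between people is still missing.

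The article condenses a fuller protocol, so a formula may exist elsewhere. But this section does state its inputs, effect, power and n, and those inputs do not support the claim made for variability.

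A reader might infer more than the documents support:
- **That 69 follows from nothing in the pilot.** It does follow, as step 2 shows, but through mean stride time.
- **That the trial is underpowered for variability.** The SDs above 0.22 are assumptions, and the baseline adjustment that the plan favours could restore the power.
- **That power is only about 14%.** That figure is for an F-test of a 10% lower group SD at 69 per arm, and the plan uses linear regression.
- **That the pilot p = .04 proves a test of group SDs.** A one-sided F-test of 266 against 112 on 5 and 5 degrees of freedom does give 0.040. But it treats repeated measures on the same six people as independent, and its two-sided value is 0.081.
- **That the 10% confuses relative and absolute change.** The 11 points are labelled absolute and reported as a pilot result. The pilot fall is 11.1/22.4, about 50% in relative terms, so the 10% was not taken from it.

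**Conclusion.** The point holds in this form: for gait variability, the outcome to which the article ties its sample size, 80% power at 69 per arm has no support in the figures given. That conclusion does not depend on how the ± values are read, because no between-person SD of individual CoVs appears on either reading.

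That the pilot CoV is a between-person figure is a strong inference from two ratios that agree closely with the printed values. That 69 was derived from mean stride time is also inferred, from a formula that the article does not name.

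The size of the problem cannot be fixed. Unadjusted power reaches 80% only if the SD of log CoV is about 0.22 or less, and the direction and size of any shortfall are unknown. The flaw concerns variability alone: the planned size is not arbitrary for gait velocity, where power is about 76% at the larger pilot SD.

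**What to change.** 1. Recompute stride-time CoV within each pilot participant from the stored walkway data. In Sample size determination, replace 22.4% and 11.3% with the mean and SD of those individual CoVs.
2. State the 10% as a relative reduction (ratio 0.90), name the formula, and restate the power or the detectable reduction for variability at the planned n. If baseline adjustment is counted on, state the correlation assumed.
3. If the individual records cannot be recovered, withdraw the 80% claim for variability and say that its power is unknown. Rest the stated power on gait velocity with its SD (10 cm/s at SD 22: about 76% at 69 per arm, unadjusted).
4. In Statistical Analysis, say that CoV is computed within each participant before the arms are compared.

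The cost is reprocessing six pilot records and rewording two sections. No extra patients are needed and no treatment or visit changes. The restated power may turn out higher or lower than 80%.

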**Method/Design:**

Double blinded randomized controlled trial with 6 months follow-up in 140 older individuals with Mild Cognitive Impairment (MCI). Participants will be randomized to the intervention group, receiving donepezil, and to the control group, receiving placebo. A block randomization by four and stratification based on fall history will be performed. Primary outcomes are improvements in gait velocity and reduction in gait variability. Secondary outcomes are changes in the balance confidence, balance sway, attention, executive function, and number of falls.

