## Methods/Design

### Design

Double blinded randomized controlled trial with 6 months follow-up in 140 older individuals with MCI. Participants will be randomized, in blocks of four, to the control and the intervention groups (Figure 3).

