### Participant Selection

Our pilot study referenced above has given us preliminary research experience with this patient population. Participants will be recruited from the Aging Brain and Memory Clinic at Parkwood Hospital. The clinical investigators will enrol an average of five (5) participants per week, thereby recruiting the 140 participants over a period of 7 months. In order to maximize enrolment possibilities, the recruitment period will be extended to 10 months if the 140 participants are not reached at month 7.

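### Enrolment is set at 140, but the sample size section calls for 150, and 140 with the stated 5% drop-out leaves fewer than the 69 per arm it requires

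*Protocol article*

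**What the plan says.** Enrolment is stated in four places in the protocol article.

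- Abstract (Method/Design): 140 individuals with mild cognitive impairment.
- Design: "Double blinded randomized controlled trial with 6 months follow-up in 140 older individuals with MCI".
- Participant Selection: five participants per week, "thereby recruiting the 140 participants over a period of 7 months". It adds that "the recruitment period will be extended to 10 months if the 140 participants are not reached at month 7".
- Sample size determination: for a 10% reduction in gait variability "with a type II error of 0.20", "69 participants in each arm will be needed for the final analysis"; then, "assuming a 5 percent drop-out rate", "75 per arm participants will need to be recruited".

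The Randomisation section fixes the ratio at 1:1, so 140 means 70 per arm and 75 per arm means 150.

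**The concern.** The number to enrol depends on which section is read. The sample size section derives one figure, and the sections that govern recruitment use a smaller one. The smaller figure is almost the evaluable requirement itself (2 × 69 = 138), so it leaves next to no room for the drop-out that the same plan assumes.

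The trial could therefore reach its recruitment goal and still have fewer evaluable participants than its own calculation asks for. Stopping at 140 could also be reported either as target met, under Participant Selection, or as ten short, under Sample size determination. That should be settled before outcome data are seen.

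**Working it through.** **Inputs, all from the protocol article**

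- Planned enrolment: 140 (Abstract, Design, Participant Selection)
- Allocation: 1:1 (Randomisation)
- Evaluable per arm: 69. Drop-out: 5%. To recruit per arm: 75. Type II error: 0.20 (Sample size determination)
- Two-sided significance level: 0.05 (Statistical Analysis)
- Recruitment rate: 5 per week (Participant Selection)

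**Step 1. The plan's own figure of 75.** Number to recruit = evaluable ÷ (1 − loss) = 69 ÷ 0.95 = 72.6, so at least 73 per arm, or 146 in total. The stated 75 is two per arm above that minimum. After 5% loss it leaves 75 × 0.95 = 71.25 per arm, which meets 69. It would still meet 69 at a loss of 1 − 69/75 = 8.0%. The figure is adequate for the stated drop-out.

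**Step 2. The planned 140.** 140 × 0.95 = 133 in total; 70 × 0.95 = 66.5 per arm. The requirement is 2 × 69 = 138. The shortfall is 138 − 133 = 5 in total, or 2.5 per arm. The largest loss that 70 per arm can absorb is 1 − 69/70 = 1.4%.

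**Step 3. The gap between targets.** 140 is 10 below the stated 150, and 6 below the strict minimum of 146. Rounding does not explain either gap.

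**Step 4. Effect on power (conditional).** The article gives no between-person standard deviation for stride time variability, so 69 cannot be re-derived. Suppose instead that 69 per arm gives exactly 80% power for an unadjusted two-sided 5% comparison of two means. The implied standardised effect, by the normal approximation, is

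d = (1.960 + 0.842) × √(2/69) = 0.477.

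Power at n per arm is Φ(d × √(n/2) − 1.960):

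| n per arm | Situation | Power |
|---|---|---|
| 66 | 140 enrolled, 5% loss, rounded down | 78.2% |
| 66.5 | 140 enrolled, 5% loss | 78.5% |
| 69 | stated requirement | 80.0% (by assumption) |
| 71.25 | 150 enrolled, 5% loss | 81.2% |

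**Step 5. Feasibility of 150.** 150 ÷ 5 = 30 weeks. Seven months is 7 × 52/12 = 30.3 weeks. At the same rate 140 takes 28 weeks.

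**The case against.** The best case for the plan is that little turns on this. Three sections agree on 140, the shortfall is 2.5 per arm, and the analysis may recover it. The Statistical Analysis section prefers baseline adjustment. If 69 came from an unadjusted comparison, which the article does not say, then 66.5 adjusted participants per arm match 69 unadjusted ones once r² = 1 − 66.5/69 = 0.036. That is a baseline–outcome correlation of about 0.19. This stands as a reason not to treat the power loss as established. It does not make 140 equal to 150.

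Reading 140 as the number of completers does not help, since Participant Selection gives it as the number recruited.

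A reader might infer three stronger things, none of which the document supports:

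- **That the drop-out inflation is wrong because 75 per arm matches 8% loss, not 5%.** The article claims no 8% loss, and recruiting two per arm above the minimum is cautious rounding.
- **That the trial as written fails to deliver its type II error of 0.20.** What is shown is that it misses its own evaluable number. Whether power falls below 80% depends on a 69 that cannot be checked and on the analysis used.
- **That recruitment must stop at 140.** Participant Selection makes 140 the goal and the trigger for an extension, but states no stopping rule. It is fair to call 140 the target; a hard stop is not written.

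**Conclusion.** The inconsistency is certain and needs no outside assumption: the enrolment target is 140 in three sections and 150 in the one that justifies the number. The retention shortfall of 133 against 138 follows directly from the stated 69 per arm and 5% loss.

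The consequence is small. Power of about 78% rather than 80% holds only if 69 per arm gives exactly 80% in an unadjusted two-sided 5% test, with d of about 0.48 back-solved. The concern is moderate: it affects the enrolment target, not the validity of the comparison.

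**What to change.** State one enrolment target in the Abstract, Design, Participant Selection and Sample size determination sections. Either route works.

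1. **Keep 140.** Rewrite the sample size section to say that 70 per arm are recruited, that about 66 per arm are expected to be evaluable after 5% loss, and that power is slightly below 80%. If a figure of about 78% is given, state its assumptions with it (69 per arm gives exactly 80%, two-sided 0.05, no covariate adjustment) until the standard deviation behind 69 is supplied.
2. **Adopt 150.** Change 140 to 150 in the Abstract, Design and Participant Selection sections, including the condition for extending recruitment. The 75 per arm needs no change.

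The first route costs only wording. The second adds ten participants and, at five per week, two weeks of recruitment (30 instead of 28), which stays within the planned seven months.
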